## Abstract

**Introduction:**

The UK government recommends that at least 75% of people aged under 64 with certain conditions receive an annual influenza vaccination. Primary care practices often fall short of this target and strategies to increase vaccine uptake are required. Text messaging reminders are already used in 30% of practices to remind patients about vaccination, but there has been no trial addressing their effectiveness in increasing influenza vaccine uptake in the UK.

The aims of the study are (1) to develop the methodology for conducting cluster randomised trials of text messaging interventions utilising routine electronic health records and (2) to assess the effectiveness of using a text messaging influenza vaccine reminder in achieving an increase in influenza vaccine uptake in patients aged 18–64 with chronic conditions, compared with standard care.

**Methods and analysis:**

This cluster randomised trial will recruit general practices across three settings in English primary care (Clinical Practice Research Datalink, ResearchOne and London iPLATO text messaging software users) and randomise them to either standard care or a text messaging campaign to eligible patients. Flu vaccine uptake will be ascertained using routinely collected, anonymised electronic patient records. This protocol outlines the proposed study design and analysis methods.

**Ethics and dissemination:**

This study will determine the effectiveness of text messaging vaccine reminders in primary care in increasing influenza vaccine uptake, and will strengthen the methodology for using electronic health records in cluster randomised trials of text messaging interventions. This trial was approved by the Surrey Borders Ethics Committee (13/LO/0872). The trial results will be disseminated at national conferences and published in a peer-reviewed medical journal. The results will also be distributed to the Primary Care Research Network and to all participating general practices.

**Trial registration number:**

This study is registered at controlled-trials.com ISRCTN48840025, July 2013.

Strengths and limitations of this studyThis trial is the first to evaluate the effectiveness of text messaging for influenza vaccine reminders in English primary care.Text messaging is cheap, quick and has shown to be effective for appointment reminders.The study requires minimal input from practices as it uses routinely collected electronic health records to gather vaccine uptake data.There may be some contamination if general practices in the standard care arm choose to send a text message.

## Introduction

Influenza morbidity and mortality causes a substantial financial burden to the National Health Service and to the UK as a whole. Influenza vaccine is safe and effective but is required annually because the circulating strain of the virus changes each year. In the UK in 2012, the Chief Medical Officer recommended that at least 75% of elderly people (aged 65+) and 75% people under 65 with certain chronic conditions (eg, chronic heart disease, diabetes, asthma, etc) should be vaccinated.^1^

While many primary care practices are achieving these targets for elderly patients (74% vaccinated in 2011/2012), those set for patients with chronic conditions are not being met and have shown no substantial increases in the past decade^2^; vaccine uptake in 2011/2012 was 51.6% across the risk groups (see online supplementary table S1). Barriers to influenza vaccination in the UK include the lack of recommendation for vaccination by a healthcare worker,^3^ lack of awareness of eligibility for vaccination,^4^ low perceived susceptibility to and severity of influenza,^3–5^ beliefs that the effectiveness of the vaccine is low, and beliefs about its side effects, safety and pain.^3^
^5^ Strategies to increase flu vaccine uptake are required.

Several randomised trials have demonstrated the effectiveness of flu vaccine reminders delivered to patients by letter, postcard or telephone.^6^
^7^ However, the use of text messaging in the NHS for appointment reminders is increasing as it is cheap, quick and effective. Text messaging is already used in roughly 30% of practices to remind patients about their flu vaccine,^8^ but there has been no trial addressing its effectiveness in this context. Trials of text messaging in the USA have shown some success as vaccine reminders,^9^ but whether there is an effect in UK primary care is unknown.

Therefore, we are performing a randomised trial of a text messaging flu vaccine reminder in patients aged under 65 who have a chronic condition (as described in online supplementary table S1). We will randomise whole primary care practices to either a text messaging campaign to eligible patients or to standard care (chosen as the comparator group because practices currently employ a variety of methods to encourage at-risk patients for influenza vaccine).^8^

## Aims and objectives

The aims of the study are (1) to develop the methodology for conducting cluster randomised trials of text messaging interventions using routine electronic health records and (2) to implement a cluster randomised trial to test the effectiveness of using a text messaging influenza vaccine reminder in achieving an increase in influenza vaccine uptake in patients aged 18–64 with chronic conditions compared with standard care.

Specific objectives are: (1) to evaluate the effect of text messaging influenza vaccination reminders in patients under 65 with chronic conditions; (2) to evaluate the feasibility of recruiting and randomising practices to a text messaging intervention; (3) to evaluate the feasibility of practice delivery of a text message intervention to eligible patients within a primary care setting and (4) to evaluate the feasibility of ascertaining practice data regarding text message delivery and flu vaccine uptake.

## Methods

### Study design

A cluster randomised trial^10^
^11^ of a text messaging influenza vaccination reminder in primary care.

### Study population

This study is taking place in English primary care, with general practices recruited from three settings: (1) the Clinical Practice Research Datalink (CPRD),^12^ a primary care database based on Vision software and covering 8% of the UK population; (2) ResearchOne, a primary care database based on TPP SystmOne software^13^ and covering 7.6% of the UK population and (3) iPLATO text messaging software users in London.^14^

### Inclusion criteria

Eligible practices must currently use a text messaging system to communicate with patients about issues other than influenza vaccination (CPRD and London practices must use iPLATO,^14^ ResearchOne practices must use TPP SystmOne text messaging software. Practices using other text messaging software will be excluded). Practices that used text messages for influenza vaccination reminders in the 2012/2013 influenza season will be excluded.

### Recruitment

Eligible practices in the CPRD (n=40) will be identified using the electronic health record and invited to the trial. All TPP SystmOne practices (n=2073) and London-based iPLATO practices (n=460) will be invited to the trial by the Primary Care Research Network. London iPLATO practices will also be contacted by iPLATO and TPP SystmOne practices will be targeted through SystmOne communications. The Primary Care Research Network^15^ will be involved in practice recruitment to ensure that the target sample size is reached.

### Sample size calculation

The sample size calculation is based on a comparison between influenza vaccine uptake in the intervention group, in which a text message influenza vaccination reminder will be sent to eligible patients, and influenza vaccine uptake in the standard care group. A cluster-level analysis of the practice-specific proportions will be undertaken and the sample size calculation estimates the number of practices required for the study. A systematic review of reminders for influenza vaccination reported that reminders (of any type) for influenza vaccine among adults increased the uptake, with an OR of 1.66, 95% CI 1.31 to 2.09).^16^ However, a text messaging vaccine reminder trial among children in the USA found only a 9% increase (RR=1.09, 95% CI 1.04 to 1.15).^9^ Therefore, we have chosen to power our study for a risk ratio of 1.075, representing an increase from 54% (uptake in the CPRD 2012/2013) to 58%.

At 90% power and 5% significance, with an ICC by general practice of 0.024 and an average of 750 eligible patients per practice, we will require 100 practices (50 per arm) to identify a 7.5% increase in vaccine uptake from 54% to 58%. To account for differences in the number of eligible patients per practice and the proportion with mobile phone numbers recorded, we have chosen to recruit and randomise 150 practices to the study.

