### Assignment of interventions

Practices will be randomised on a 1:1 basis to the intervention and standard care groups. We will use block randomisation within each setting. In the CPRD and ResearchOne, we will stratify by region. The allocation sequence will be generated by an independent statistician who will be blinded to practice name and the allocation sequence will be concealed from the study team. Once practices have been allocated, the trial coordinator will inform practices about their allocation and distribute study materials.

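### Sample size: the stated inputs give about 160 to 166 practices for 90% power, not 100, so one of the printed figures needs correcting

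*Protocol article*

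**What the plan says.** All the relevant figures are in the article's section on the sample size calculation.

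- Error rates: "At 90% power and 5% significance". Sidedness is not stated.
- Effect: "we have chosen to power our study for a risk ratio of 1.075", described as "an increase from 54% (uptake in the CPRD 2012/2013) to 58" percent.
- Clustering: "with an ICC by general practice of 0.024" and "an average of 750 eligible patients per practice".
- Result: "we will require 100 practices (50 per arm) to identify a 7.5% increase in vaccine uptake from 54% to 58" percent.

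The section then raises the target to 150 practices, to cover variation in the number of eligible patients per practice and in the share with a recorded mobile number. Allocation is equal: "Practices will be randomised on a 1:1 basis to the intervention and standard care groups" (Assignment of interventions). The planned analysis is a t test on practice-specific proportions that takes practice size into account (Statistical methods). The calculation claims no variance reduction from stratification or baseline adjustment.

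**The concern.** Every input and the result are printed together, so the calculation can be repeated, and it does not return 100. At an ICC of 0.024 with several hundred patients per practice, nearly all the variance of a practice proportion lies between practices. The number of practices therefore drives power, and 50 per arm is too few for a 4-point difference at 90%.

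Two statements depend on this. One is the 90% power attached to 100 practices, which would be the natural benchmark if recruitment stopped between 100 and 150. The other is the purpose given for the additional 50 practices. If the inputs are right, those 50 do not fully meet the basic requirement and leave nothing for unequal practice size or missing phone numbers.

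**Working it through.** **Inputs** (Sample size calculation): p1 = 0.54; p2 = 0.58 (or 0.54 × 1.075 = 0.5805); power 90%; alpha 5%, taken as two-sided; ICC ρ = 0.024; m = 750 patients per practice; equal arms.

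**Attempt to reproduce 50 per arm**

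1. Individually randomised size per arm: n = (1.960 + 1.2816)² × (0.54 × 0.46 + 0.58 × 0.42) / 0.04² = 3,231.
2. Design effect: 1 + (750 − 1) × 0.024 = 18.976.
3. Practices per arm: 3,231 × 18.976 / 750 = 81.7, so 82 per arm and 164 in total.

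The stated 50 per arm is not reproduced.

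**Other readings of the same inputs**

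| Reading | Practices per arm |
|---|---|
| Two-sided 5%, 90%, 58% | 81.7 |
| Same, pooled variance | 81.8 |
| Same, continuity correction | 83.1 |
| Same, t distribution on practice proportions | 83 |
| Same, exact risk ratio 1.075 (58.05%) | 79.7 |
| Same, coefficient-of-variation cluster formula (k = 0.143 from the ICC) | 89.6 |
| Unlimited patients per practice (3,231 × 0.024) | 77.5 |
| One-sided 5%, 90% | 66.6 |
| Two-sided 5%, 80% | 61.1 |
| One-sided 5%, 80% | 48.1 |

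No reading at the stated 90% power gives 50. The only one close to it needs both a one-sided test and 80% power, and the second contradicts the text. Reading 0.024 as a coefficient of variation, as its square, or as a between-practice variance gives about 8, 104 and 321 per arm, so none of these explains the figure either.

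**Power at the stated and planned numbers** (two-sided, ICC 0.024, equal practice sizes)

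SE = √[(0.2484 + 0.2436) × 18.976 / (K × 750)] for K practices per arm.

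- K = 50: SE = 0.0158; z = 0.04 / 0.0158 = 2.535; power 71.7% (70.9% with t). At 58.05%: 72.8% (72.0% with t). Difference detectable at 90% power: about 5.1 points.
- K = 75: SE = 0.0129; z = 3.105; power 87.4% (87.0% with t). At 58.05%: 88.2% (87.8% with t). Difference detectable at 90% power: about 4.2 points.
- One-sided 5%: 81% at K = 50 and 93% at K = 75; 134 practices needed in total.

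**What would reproduce 50 per arm**

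Solving 3,231 × [1 + 749ρ] / 750 = 50 gives ρ = (37,500 / 3,231 − 1) / 749 = 0.0142. With that ICC the design effect is 11.6, and 75 per arm give SE = 0.0101, z = 3.96 and power of about 98%. Keeping ρ = 0.024, an intervention uptake of about 59.1% would be needed instead.

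**The case against.** The strongest objection concerns what the mismatch proves. It shows that the inputs and the result disagree, not which is wrong. A reader might infer that the ICC of 0.024 is right, so that the trial has no reserve and the 50% margin is illusory. The document does not settle that. If 0.024 is a reporting error for something near 0.014, then 100 practices do give 90%, 150 give about 98%, and the margin is real. The shortfall is conditional on the printed ICC. This objection stands.

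Second, 150 practices are to be randomised, so the 71 to 73% belongs to a sample size the trial does not plan to use. At 150 the shortfall against 90% is 2 to 3 points. This also stands, and it limits the practical harm. It does not rescue the sentence.

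Third, a reader might infer a larger loss at 150 from unequal practice sizes. Weights proportional to size and a coefficient of variation of size of 0.5 to 0.6 give a design effect of 1 + [(1 + CV²) × 750 − 1] × 0.024, which is 23.5 to 25.5, and power of 76 to 80%. The document gives no such coefficient and does not specify those weights. Under an unweighted t test on practice proportions the loss is small: the between-practice share of variance is 0.024 / (0.024 + 0.976 / 750) = 95%. Replacing 1/m by (1 + CV²)/m leaves power at about 86 to 87%. The lower figures are assumption-dependent and cannot be read off the plan.

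Two other defences fail. Stratified randomisation might reduce variance, but the calculation claims no reduction, and going from 81.7 to 50 per arm would need about 39% of the variance removed (1 − 50 / 81.7). Nor is this an effect of condensing a fuller protocol: inputs and result are both printed, and a fuller document could only show which one is wrong.

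**Conclusion.** The sentence is wrong as written. With its own inputs and a two-sided 5% test, 90% power needs about 160 to 166 practices, against the 100 stated. Power is about 71 to 73% with 100 practices and about 87 to 88% with 150, before any allowance for unequal practice size or missing mobile numbers. Two-sided testing is an assumption; under a one-sided test 100 is still too few (134 needed), although 150 would then suffice. The statement that the extra practices provide a margin fails only if the ICC of 0.024 and two-sided testing both hold. The conclusion that figures in this section contradict each other needs neither condition.

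**What to change.** Check the source calculation, establish which figure is wrong, state the sidedness of the test, and restate the sentence in one of two ways.

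(a) If the ICC of 0.024 stands (two-sided test): state that about 164 practices are needed for 90% power, and that the planned 150 give about 87% for 54% versus 58%, or 90% for a difference of about 4.2 points, with equal practice sizes. Drop the statement that the extra 50 practices cover unequal practice size and missing mobile numbers.

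(b) If 0.024 was misreported: print the ICC actually used (about 0.014 reproduces 50 per arm). The account of the margin at 150 can then stay.

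In either case, any power figure quoted for unequal practice sizes should name the weighting and the coefficient of variation it assumes.

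The cost is wording only. Under (a) the stated power becomes slightly less favourable. Neither version requires more practices or a change to the design.

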### Outcomes

The aims of the study are (1) to develop the methodology for conducting cluster randomised trials of text messaging interventions using routine electronic health records and (2) to implement a cluster randomised trial to test the effectiveness of using a text messaging influenza vaccine reminder in achieving an increase in influenza vaccine uptake in patients aged 18–64 with chronic conditions compared with standard care.

To address aim 2, we will examine the proportion of eligible patients who received the influenza vaccination by 31 December 2013 (primary outcome). This will be stratified by risk group, age and sex. A secondary outcome will be the proportion of eligible patients who were sent a text message to remind them about flu vaccine.

To address aim 1, we will measure the following as secondary outcomes:
Practice recruitment rate (based on the number of practices invited across three trial settings, and the number recruited);The proportion of intervention practices and standard care practices that sent a text message to eligible patients;The proportion of practices reporting any problems with delivering the message;The availability of data to examine text message receipt and vaccine uptake in each risk group;The time and cost required to gather data.

In the patient substudy, we will also examine the acceptability of text messaging to patients, by measuring the proportion of patients who reported problems with the text message.

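### The step from 100 to 150 practices rests on no mobile-coverage figure and leaves no reserve: on the stated inputs, 150 practices give about 87% power before any dilution

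*Protocol article*

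**What the plan says.** All references are to the protocol article.

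- **Sample size calculation, effect:** "we have chosen to power our study for a risk ratio of 1.075, representing an increase from 54% (uptake in the CPRD 2012/2013) to 58" per cent.
- **Sample size calculation, other inputs:** "At 90% power and 5% significance, with an ICC by general practice of 0.024", and "an average of 750 eligible patients per practice". The stated result is 100 practices, 50 per arm.
- **Sample size calculation, allowance:** the number is then raised for differences in practice size and for "the proportion with mobile phone numbers recorded, we have chosen to recruit and randomise 150 practices to the study". No coverage figure, size variation or formula is given for this step.
- **Outcomes:** the primary outcome is "the proportion of eligible patients who received the influenza vaccination by 31 December 2013 (primary outcome"). It is not restricted to patients with a mobile number.
- **Sensitivity and subgroup analyses:** the primary analysis is by intention to treat. A per-protocol analysis is planned to deal with contamination.
- **Strengths and limitations:** "There may be some contamination if general practices in the standard care arm choose to send a text message". Contamination is not among the reasons given for going to 150.
- **Inclusion criteria:** practices that texted about flu vaccination in 2012/2013 are excluded.

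**The concern.** A patient with no recorded mobile number cannot receive the intervention but still counts in the primary outcome. Such patients reduce the difference between arms rather than the number of patients analysed. If a share p of eligible patients can be texted, the intention-to-treat difference is p times the difference among those texted, and the number of practices needed grows as 1/p². The 50 extra practices are offered as the allowance for this, for unequal practice sizes as well, and on top of a base of 100. If the base is too small, the extra practices are used up before either allowance begins.

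What is at stake is how a null result would be read. Without a sound power statement, it could reflect limited reach as easily as an ineffective message.

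**Working it through.** **Inputs from the protocol:** 54% v 58%; ICC 0.024; 750 eligible patients per practice; 90% power; 5% significance (taken as two-sided, since sidedness is not stated); 1:1 allocation; 150 practices, so 75 per arm. **Assumptions, not in the protocol:** mobile coverage p, shown from 60% to 100%; equal practice sizes unless stated; equal baseline uptake with and without a number.

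**1. The stated 100 practices.** Two proportions, 54% v 58%, 90% power, two-sided 5%: 3,235 patients per arm. Design effect = 1 + (750 − 1) × 0.024 = 18.976. Practices per arm = 3,235 × 18.976 / 750 = 81.8, so 82 per arm and 164 in total.

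Variants do not rescue the figure:
- 58.05% in place of 58%: 80 per arm.
- Continuity correction with 58%: 84 per arm.
- Hayes–Bennett formula (k = 0.143 from the ICC): about 90 per arm.
- One-sided 5% at 90% power: 67 per arm.
- One-sided 5% at 80% power: 48 to 49 per arm. Only this variant comes near 50, and it contradicts the stated 90%.

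**2. Power before any dilution.** SE of the difference = √[(0.54 × 0.46 + 0.58 × 0.42) × 18.976 / (750 × K)], with K practices per arm.
- K = 50: SE 0.0158, power about 71% (t test).
- K = 75: SE 0.0129, 0.04 / 0.0129 = 3.10, power about 87%.

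Unequal practice sizes lower this. With an assumed coefficient of variation of 0.5 and design effect 1 + [(0.5² + 1) × 750 − 1] × 0.024, power at K = 75 is about 79 to 80%.

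**3. If the 4 points apply only to patients who can be texted.** Difference = 0.04 × p, 75 per arm. The last column accepts the stated claim that 100 practices give 90%, so that the effect of coverage can be seen apart from the base-size error.

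| Assumed coverage p | Difference (points) | Power, stated inputs (t test) | Same, normal approximation | Power if 100 practices did give 90% |
|---|---|---|---|---|
| 100% | 4.0 | 87% | 87% | 98% |
| 90% | 3.6 | 79% | 80% | 95% |
| 80% | 3.2 | 69% | 70% | 89% |
| 70% | 2.8 | 58% | 58% | 79% |
| 60% | 2.4 | 45% | 46% | 66% |

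On the last column's premise, a factor of 1.5 keeps 90% power down to p = √(100/150) = 0.816, if nothing is spent on unequal sizes. On the stated inputs there is no such margin, because 150 is already below 164.

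Texting in the standard care arm multiplies the difference by (1 − share of control practices texting). As illustrations only, at 80% coverage a share of 10% gives about 60% power and 20% about 51%. At 70% coverage the figures are about 49% and 41%.

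**4. If 58% already means all eligible patients.** Coverage is then inside the effect and does not call for more practices. The risk ratio needed among texted patients is 1 + 0.075/p: 1.083 at 90%, 1.094 at 80%, 1.107 at 70% and 1.125 at 60%. It passes 1.09 when p falls below 0.075/0.09 = 0.83.

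**5. If coverage is treated as fewer patients per practice.** With 450 in place of 750, the requirement is 3,235 × (1 + 449 × 0.024) / 450 = 84.7 per arm, about 3% more. This reading does not lead to a factor of 1.5 either.

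**The case against.** Adding practices is a legitimate way to offset dilution, and the protocol does not say that it treated missing numbers as lost patients. Both points stand. The fault is that the size of the allowance is not tied to any coverage figure and starts from a base that is too small.

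A reader might infer that power is simply far below 90% because of phone coverage. The document does not support that. It gives no coverage figure, and the calculation compares uptake in whole groups with a risk ratio set below the cited 1.09, so 58% may already allow for incomplete reach. Multiplying by p would then count dilution twice. The allowance sentence points the other way, so the text is ambiguous. Part of the shortfall in the table also belongs to the base-size error and not to coverage, as its last column shows.

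A reader might also take the roughly 30% of practices said in the Introduction to text about flu vaccination as the contamination rate. It is not one, since practices that did so in 2012/2013 are excluded. The 10% and 20% above have no source.

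On plausibility, a risk ratio of 1.107 lies within the cited interval of 1.04 to 1.15, and the cited odds ratio of 1.66 for reminders of any type would take 54% to about 66%. The required effect is therefore not implausible; it is larger than the one text-message estimate cited.

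Finally, the proportion of eligible patients sent a text is a secondary outcome and reminder type is extracted, so reach will be visible. But being sent a text happens after allocation and cannot define a randomised comparison, and a per-protocol analysis has the same weakness.

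**Conclusion.** The point holds in two parts of different strength.

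**Firm:** on the stated inputs with a two-sided 5% test, about 164 practices are needed for 90% power. The planned 150 give about 87% with equal practice sizes, full reach and no contamination. The extra 50 therefore hold no reserve for mobile coverage.

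**Conditional:** if 58% is uptake when every patient can be texted, power falls to about 79%, 69%, 58% and 45% at assumed coverage of 90%, 80%, 70% and 60%, and lower still if control practices text. If 58% is uptake across all eligible patients, power stays at about 87%, but the effect needed among texted patients exceeds the cited risk ratio of 1.09 once coverage is below about 83%, given equal baseline uptake in patients with and without a number.

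On neither reading is the factor of 1.5 shown to be a sufficient allowance for coverage.

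**What to change.** 1. State whether 58% refers to all eligible patients or only to those who can be texted.
2. Restate power for 150 practices as about 87% undiluted on the stated inputs. Correct the base of 100 as a separate matter. Then give a conditional range over assumed coverage, with the assumed variation in practice size and any assumed texting by control practices shown.
3. Stop presenting the extra 50 practices as a sufficient allowance for phone coverage.
4. Keep all eligible patients as the primary population.
5. Extract a yes/no flag in both arms for a mobile number recorded before randomisation, and make uptake among flagged patients a secondary comparison. The flag predates allocation, so the comparison remains randomised and is not diluted by missing numbers. It does not restore power for the primary comparison.

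The cost is a less favourable power statement and one non-identifying data field, which some suppliers may be unable to provide.
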